***Results of the optimisation and pilot RCT study***

Intervention optimisation involved collaboration with one secondary school, and PPI with the Advice Leading to Public Health Action (ALPHA) group of young people based at the DECIPHer Centre in Cardiff, trained to provide advice on public health research, as well as a group of policy/practice stakeholders. This elaborated Positive Choices from a basic description to a fully specified intervention with materials. This was successful and all components were successfully feasibility-tested in the collaborating school. The curriculum was refined and broadened from that originally planned to ensure that it provided comprehensive RSE while still addressing all topics in the protocol. Social-marketing campaigns segmented student audiences only on age, informed by PPI with teachers and students suggesting that other targeting would stigmatise those students. Review of sexual and reproductive health services was reoriented away from what was originally planned as SEF consultancy for schools, towards a guided school self-audit to increase cost-efficiency and school capacity for sustainability.

In the subsequent pilot RCT across 6 schools, all criteria for progression to phase III were met. All schools were randomised, 4 to intervention and 2 to control, and remained in the study. Student response rates in intervention and control groups were 89% and 84% at baseline, and 89% and 82% at follow-up. The intervention was implemented with fidelity in 3 intervention schools with limited data from 1 school preventing assessment of fidelity. Around two-thirds of students reported awareness of the intervention, and around 80% of these students and all staff interviewed indicated acceptability. Positive Choices students reported significantly more comprehensive coverage of RSE topics than controls. Linkage of self-report and registered births and terminations was feasible but, unsurprisingly given students’ ages and national trends, there were no registered births or terminations among trial participants.

Measures were assessed as reliable and economic evaluation methods were feasible. Staff interviews suggested that senior leadership team commitment was critical to successful delivery. Schools struggled with the short time between being allocated to the intervention group (July in the pilot) and then being required to start delivering the intervention (September in the pilot). To increase efficiency and school capacity to sustain the intervention, a train-the-trainer model (with SEF training selected school staff to train other staff) was recommended. Students reported Positive Choices enabled more open conversations about sexual health and raised awareness of sexual rights and responsibilities. Staff reported that the intervention enhanced student engagement. Parents found the intervention acceptable. No student harms were apparent.

PPI with youth and policy/practitioner stakeholders, and consultation with the study steering committee (SSC) supported the view that Positive Choices should now be subject to a phase-III RCT. Stakeholder workshops suggested considerable interest in whole-school and social-marketing interventions as a means to implement new statutory requirements for schools to implement relationships, sex and health education. PPI with policy/practice stakeholders recommended: a longer lead-in from allocation to intervention and delivery; intervention costs being met by schools or local authorities; and including a focus on DRV as part of the intervention. PPI with the policy/practice stakeholders and the ALPHA youth group also recommended a change in the primary outcome from pregnancy to lack of sexual competence at first sex. The rationale was that: while teenage pregnancy rates are declining, other risks such as STIs and DRV are increasing; lack of sexual competence at first sex is an excellent indicator of overall sexual risk that is strongly associated with subsequent risk in adolescence or adulthood of STI among young women, unplanned pregnancy, ever having experienced non-volitional sex and sexual dysfunction;(1) and lack of sexual competence at first sex is relevant to all young people regardless of gender and sexual orientation whereas pregnancy is applicable only to heterosexual intercourse among girls.

***Changes to intervention and research methods for phase III protocol***

The original pilot RCT protocol made clear that in the pilot the curriculum would only target students in year 9, whereas in phase III the curriculum will target students as they moved from year 9 into year 10 (and this remains our plan). In the phase-III RCT, the intervention will also address DRV, informed by our consultation with policy/practice stakeholders in the pilot RCT, and by our finding from the pilot RCT of Project Respect to prevent DRV that this outcome is best addressed as part of a broader RSE intervention rather than through a stand-alone intervention.(42) The incorporation of DRV content into Positive Choices is supported by evidence that sexual health education can effectively reduce DRV and sexual assault.(43) To address DRV, existing additional content on DRV will be incorporated into the Positive Choices curriculum. This element from Project Respect was informed by evidence of effective DRV prevention, notably the Safe Dates and Shifting Boundaries trials.(44, 45) As recommended in the Positive Choices pilot RCT, staff training will use a train-the-trainer model whereby school lead staff will be trained and cascade this to colleagues. Training on running school health promotion councils will be reoriented to consist of an extended workshop with senior leadership teams in each school to build commitment and ensure good planning in the start-up phase. We will also review methods and materials to assess need for refinements in the context of COVID-19. The production of the curriculum materials for year 10 and the integration of existing material on DRV into Positive Choices materials will be led by SEF and the research team in the start-up phase in collaboration with the ALPHA youth group and a policy/practice stakeholder group, with sign-off by the SSC.

Regarding research methods, the pilot found that schools would be more ready to deliver the intervention if there were a longer period from random allocation to delivery. We therefore plan a start-up phase between notifying schools whether they have been allocated to the intervention group (March 2022) and schools beginning to deliver the intervention to students (September 2022). During this phase, schools will be trained and prepare for delivery by planning timetabling and staffing of lessons and other activities.

The primary outcome piloted in the pilot RCT was pregnancy assessed via registered births and terminations. However, pregnancy does not reflect the areas of greatest sexual health need in terms of current trends, and powering a trial on this outcome would require an unfeasibly large school sample.(46) The most recently reported prevalence of conceptions among girls aged 15-17 is 1.8%.(13) Furthermore, as raised by PPI stakeholders, this outcome is too narrow, focusing on one risk and relevant only for girls and heterosexual sex. Instead, we will use a self-reported measure indicating lack of competence at first sex as our primary outcome,(1, 2) which was the strong preference of the ALPHA young researchers’ group and the policy/practice PPI stakeholder group. This outcome can be reliably measured and is strongly associated with subsequent multiple sexual health outcomes as described above.(1, 2) The measure was piloted in the Positive Choices pilot RCT where it performed well in terms of completion (88%) and inter-item reliability (ordinal alpha=0.74). All of the above refinements are informed by the pilot studies of Positive Choices and Project Respect, do not reflect fundamental changes to intervention theory or approaches and so require no additional piloting.

***Rationale and aims***

The above evidence indicates that Positive Choices meets a clear, evidenced, long-term need in terms of high prevalence of non-competence at first sex, STIs, unintended pregnancies, non-volitional sex, sexual violence and DRV, all of which are associated with major social and economic costs. Positive Choices is informed by previous systematic reviews(22-27) and by whole-school and social-marketing interventions with strong evidence of effectiveness(36-38, 44, 45, 47, 48) and has been successfully piloted. The phase-III RCT will be informed by learning from the pilot RCTs of the Positive Choices and Project Respect interventions, and be the first UK RCT of a whole-school social-marketing intervention. This will generate evidence of scientific importance and policy relevance, addressing a key evidence gap as to whether whole-school social-marketing interventions are an effective means of promoting sexual health in the English context. Relationships, sex and health education becoming statutory in English schools from September 2020 will add to the feasibility of recruitment and to the policy importance of the trial.

There are major potential public health benefits and potential benefits for participating individuals arising from the prevention of the adverse sexual health outcomes listed above. The pilot and previous studies suggest that participants are unlikely to experience increased sexual or other risks from the intervention or research.(26) In the unlikely event of the intervention generating harms, these would be identified via our surveys, qualitative research and monitoring of safeguarding concerns and serious adverse events (SAE) described below. We will maximise retention, minimise disruption to schools and ensure data quality by employing strategies we have previously used, such as: close liaison between a named researcher and school day-to-day lead to identify convenient times and places for research, and identify problems early; and compensating schools for the costs arising from their participation in research activities.

The research aims to conduct a phase-III RCT (50 schools) to examine the implementation, effectiveness, cost-effectiveness and mechanisms of the Positive Choices intervention and answer the following research questions:

1. What is the effect of the Positive Choices intervention in intention-to-treat analyses on student-reported measures of non-competent first sex (primary outcome), and various pre-hypothesised secondary outcomes and intermediate outcomes?

2. Where plausible, are these associations moderated by student gender, sexual orientation, ethnicity or socio-economic status (SES), or by school-level GCSE attainment or local deprivation?

3. Are associations greater in on-treatment analyses accounting for intervention fidelity?

4. What does the intervention cost and is it cost-effective?

5. Is the intervention delivered with good fidelity, reach and acceptability and how does this vary between schools and students?

6. What is usual treatment in control schools?

7. What do qualitative data suggest about implementation processes/intervention mechanisms and how these might vary between schools or students?

8. What do the trial findings overall suggest about the intervention theory of change and the potential for the intervention to be delivered and be effective elsewhere?

***Objectives***

a) To recruit 50 schools for the RCT by December 2021.

b) To undertake baseline surveys of students in year 8 (age 12/13 years) and randomise schools by March 2022.

c) To refine the intervention so that it includes a year-10 curriculum and addresses other points identified in the pilot phase, informed by consultation with youth and policy/practice PPI stakeholders by July 2022.

d) To prepare schools for implementation via start-up meetings and SEF and internal staff training by July 2022.

e) To implement the intervention over the 2022/23 and 2023/24 school years by July 2024.

f) To conduct the economic and process evaluations by July 2024.

g) To undertake follow-up surveys of students at the start of year 11 (age 15/16) at 33 months post-baseline by December 2024.

h) To analyse data to address the above research questions and draft the study report by 31 March 2025.

i) Informed by consultation with youth and policy/practice PPI stakeholders, to engage in knowledge exchange and assess potential scale-up from December 2024.

**Methods**

***Design***

We will conduct a superiority, phase-III cluster parallel-group RCT to assess whether incorporating Positive Choices into school provision is more effective than usual provision (see figure 1). The trial will comprise 50 schools (minimum 6440, maximum 8500 students) allocated 1:1 to intervention/control assessing primary and secondary outcomes at 33 months using primary intention-to-treat analyses, and using realist approaches to assessing contextual variations in implementation, mechanisms and outcomes.

***Settings***

Positive Choices is intended to be deliverable in all English secondary schools (including faith schools, free schools, academies and private schools) excluding pupil referral units, schools for those with special educational needs and disabilities, and schools with ‘inadequate’ Ofsted inspections (which would lack the capacity to deliver until they gain an improved inspection report). This focus on all schools reflects the universal approach that the intervention takes, which recognises that population-level impacts on most sexual health outcomes cannot be achieved through targeted interventions because of the normal distribution of population risks.(19, 49) The trial will aim to recruit a representative (in terms of school type, GCSE attainment and Income Deprivation Affecting Children Index) sample of the above schools from across southern and central England.

***Study population***

The study population is defined as students aged 12-16 years moving from year 8 into year 11 during the trial. The majority of these students will have received the intervention in years 9-10. This age-group is targeted because: proximal risk factors for adverse sexual health outcomes are manifesting,(49) prevention is not too late; and RSE is acceptable.(37, 50, 51) PPI suggests provision to year 11 students is unfeasible because of GCSE preparation. Outcomes will be analysed among students reporting data at 33-month follow-up with any missing baseline data on socio-demographic characteristics or age of sexual debut being imputed based on responses at follow-up. No students deemed competent to consent by schools will be excluded from research recruitment and consent procedures unless parents withdraw them from the research. Those consenting to participate who have mild learning disabilities or limited English will be supported to complete the questionnaire by researchers.

***Analytic sample and sample size***

We calculate that, for 80% power with 5% significance, conservatively assuming: a sample of 140 students per school; drop out of 2 schools per arm; 80% student survey response rate at follow-up; an intra-cluster correlation coefficient (ICC) of 0.015 for our primary outcome; and prevalence of this outcome of 9% among those in the control arm, we will require 25 schools per arm to detect a 36% reduction in the primary outcome (giving a prevalence of 5.85% in the intervention arm). The minimum analytic sample for outcome assessment in the RCT will therefore be approximately 6440 students providing follow-up data at 33 months. Repeating this power calculation for the originally intended primary outcome of conceptions (where the prevalence among female controls would be around 2%)(13) would require >100 schools per arm.

These estimates are informed by research and PPI. We assume 140 students per school informed by our recent INCLUSIVE trial.(52) This is a conservative assumption for the Positive Choices trial because the average year group has now risen to 190 and so assuming an 80% response rate (again informed by the Positive Choices pilot and previous studies(42, 52-54)) this would comfortably provide over 150 students.(55) Two schools dropping out is also a conservative assumption given our previous trials have experienced no drop outs.(42, 52, 53) Regarding ICCs, no data are available on school-level clustering of lack of sexual competence at first sex but we would expect this to be very similar to ICCs for non-use of contraception at first sex, which are reported as 0.01(56, 57) so a conservative assumption of 0.015 for this study is reasonable.

Our assumption about prevalence of the primary outcome among controls is also informed by the literature. Around 25% of 15-16 year-olds are sexually active compared with 7% of 12-13 year-olds.(58) Therefore, between baseline and follow-up, we would expect 18% of students to become sexually active. Data from young people participating in the third Natsal sexual behaviour survey suggest that, among those aged 15-16 years, around half lack sexual competence at first sex.(1, 2) Therefore, we would expect around half of trial participants who become sexually active by follow-up (i.e. 9% of all participants) will experience non-competent sexual debut.

Finally, our assumed minimal effect on reducing non-competent first sex by 36% represents an effect of public-health significance informed by consultation with policy stakeholders (personal communication [name] 2019). Furthermore, this magnitude of effect is in line with those reported for similar measures from trials of the interventions which have informed Positive Choices. The Safer Choices RCT reported less frequent intercourse without a condom among the intervention group than controls by a ratio of adjusted means of 0.63 (P=0.05). As reported earlier, Safer Choices students were more likely to use condoms by an OR=1.68 and more likely to use effective contraception by an OR=1.76 than controls(36-38). The Children’s Aid Society Carrera programme RCT reported increased use of effective contraception at last sex by an OR=2.37.(39)

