**SUPPLEMENTARY MATERIAL 4: POSITIVE CHOICES RCT AND SECONDARY ANALYSIS PARTICIPANT FLOW**

Schools invited

N=2845

Schools not recruited

N=2795

Schools recruited and signed consent form to participate

N=50

Schools allocated to control

N=23

Endline student response rate = 3146/4035 (78.0%)

Schools allocated to intervention

N=22

Endline student response rate = 3122/4010 (77.9%)

Schools allocated to intervention but dropped out

N=1

Schools allocated to intervention

N=24

Baseline student response rate (pre-allocation) = 3578/4511 (79.3%)

Schools allocated to control

N=25

Baseline student response rate (pre-allocation) = 3392/4506 (75.3%)

Schools allocated to control but dropped out

before endline N=2

Schools allocated to intervention but dropped out before endline

N=2

Combined intervention and control samples

Overall endline student response rate = 6268/8035 (78.0%)

Students matched to baseline response

Matching rate = 4601/6268 (73.4%)

Students with no corresponding baseline response

Non-match rate: 1667/6268 = 26.5%

Outcome applicable and completed question on outcome (see Table 3 - Overall Sample Size-)

Outcome not applicable or did not complete question

Complete data for all variables in model (see Table 3 - Sample size)

Missing data for at least one variable in model

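### The printed target effect does not match itself: a 36% reduction from 9% is 5.76%, while 5.85% is a 35% reduction, and the stated 80% power fits only the former (minor)

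*Combined protocol and SAP*

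**What the plan says.** The section on analytic sample and sample size sets its target "for 80% power with 5% significance". It assumes "a sample of 140 students per school; drop out of 2 schools per arm; 80% student survey response rate at follow-up", an ICC of 0.015 and a control prevalence of 9%. From these it concludes that 25 schools per arm are needed "to detect a 36% reduction in the primary outcome (giving a prevalence of 5.85% in the intervention arm"). It then states: "The minimum analytic sample for outcome assessment in the RCT will therefore be approximately 6440 students providing follow-up data at 33 months". The Design section repeats the figure: "The trial will comprise 50 schools (minimum 6440, maximum 8500 students) allocated 1:1 to intervention/control".

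Two later paragraphs of the sample-size section bear on how to read this. One defends 140 per school as conservative, because an average year group of 190 at an 80% response rate would yield more than 150 students. The other justifies the target effect and again gives it as 36%.

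**The concern.** The target effect on the primary outcome appears as two values in one sentence, and they differ. The gap is small in absolute terms (0.09 percentage points), but it falls where the design has almost no slack, so the choice of value decides whether the stated power is met. A reader who wants to know what the trial was designed to detect, for example when interpreting a null result, cannot tell whether the benchmark is 36% or 35%.

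A second, smaller difficulty is that 140 students per school and an 80% response rate are listed side by side as if both were separate inputs. Nothing in that sentence says whether 140 is before or after non-response. A reader who applies the 80% to the 140 arrives at a different sample and a different power from those intended.

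**Working it through.** **Inputs**, all from the section on analytic sample and sample size: control prevalence p₁ = 0.09; relative reduction 36%; printed intervention prevalence 0.0585; 25 schools per arm less 2 for drop-out, so c = 23; m = 140 per school; ICC = 0.015; alpha 5%. Sidedness is not stated, and two-sided is assumed.

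**1. The planned sample.** 2 × 23 × 140 = 6440. This reproduces the protocol's figure exactly, with no further factor for non-response.

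**2. What 140 means.** The protocol's own comparison is 190 × 0.80 = 152 responding students, set against 140. That comparison makes sense only if 140 also counts respondents. The 6440 is likewise described as students with follow-up data. So 140 is net of non-response.

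**3. The target effect.**
- 36% reduction: 0.09 × (1 − 0.36) = 0.0576, or 5.76%.
- Printed prevalence: 1 − 0.0585/0.09 = 0.350, or a 35% reduction.

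**4. Power.** The design effect is 1 + (m − 1) × ICC = 1 + 139 × 0.015 = 3.085. The effective sample per arm is 23 × 140/3.085 = 3220/3.085 = 1044. With SE = √{[p₁(1 − p₁) + p₂(1 − p₂)]/1044} and power = Φ(|p₁ − p₂|/SE − 1.96):

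| Intervention prevalence | Difference | SE | Ratio | Power |
|---|---|---|---|---|
| 5.76% (36% reduction) | 0.0324 | 0.01142 | 2.84 | 81.0% |
| 5.85% (35% reduction) | 0.0315 | 0.01146 | 2.75 | 78.5% |

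With a pooled variance the figures are 80.9% and 78.4%. The first row reproduces the stated 80%.

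**5. Smallest detectable reduction at 80% power** (pooled variance). With 23 × 140 per arm it is 35.6% (prevalence 5.79%), which rounds to the stated 36%. With all 25 schools retained it would be 34.3% (5.91%). Neither calculation leads to 5.85%.

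**6. Schools needed at 5.85%.** The requirement is 23.95 per arm, so 24 analysed (80.2% power) and 26 recruited after allowing for 2 drop-outs. At 5.76% it is 22.5, so 23 analysed and 25 recruited, as the protocol states.

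**7. Consequence of misreading 140.** If a reader applies 80% again, m = 112. The total becomes 46 × 112 = 5152, the design effect is 1 + 111 × 0.015 = 2.665, and the effective sample per arm is 2576/2.665 = 967. Power at 5.76% is then about 77.9%.

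**The case against.** The strongest reply is that this is a slip in a bracket. The 36% is stated twice and given its own justification, whereas 5.85% appears once as a figure derived from it. Taken at 36%, the number of schools, the cluster size, the ICC, the power and the 6440 all fit together. At 5.85% the shortfall is about 1.5 points, and it depends on the formula: a calculation that assumes a common between-school coefficient of variation in both arms gives 82.5% even there. All of this stands, and it is why the point is minor. It does not make the two figures agree. The protocol specifies an ICC and not a coefficient of variation. The other two-sided calculations tried with 23 schools of 140 (pooled and unpooled variance, arcsine, log risk ratio, log odds ratio, t-based) put power at 5.85% between 76.7% and 78.8%.

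Three stronger readings are tempting, and the documents do not support them.

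- *That 6440 ignores non-response.* The comparison with a year group of 190 shows that the allowance is already inside the 140.
- *That true power is nearer 75%.* That figure appears only if non-response is taken off a second time and the 5.85% is used as well.
- *That the trial missed its own minimum.* The participant flow in Supplementary Material 4 reports "Overall endline student response rate = 6268/8035 (78.0"%), which is below 6440. That is an achieved result, and the planning figure is given as approximate. A shortfall of 172 students (2.7%) does not show that the plan was wrong, and no power calculation for the achieved sample is called for.

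**Conclusion.** The mismatch is certain and rests on arithmetic alone: 36% and 5.85% cannot both describe the target effect. Its effect on power is modest, at about 81.0% for 5.76% against about 78.5% for 5.85%. The claim of 80% power with 25 schools per arm is therefore supported for 36% and not for the printed prevalence.

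The power figures assume a two-sided test, equal school sizes, an ICC of 0.015 in both arms and a normal approximation. A t reference on 44 degrees of freedom would lower them to 79.2% and 76.7%, and a one-sided 5% test would put both above 80% (about 88% and 86%). The protocol does not say which formula it used, but the reproduction in steps 4 and 5 makes 36% with 5.76% the likely intention.

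The status of 140 is a question of wording. The intended meaning can be recovered from the following paragraph but is absent from the sentence that lists the inputs. Severity: minor.

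**What to change.** 1. In the section on analytic sample and sample size, replace 5.85% with 5.76%. This agrees with the 36% repeated in the effect-size justification and with the stated power. If 35% and 5.85% were meant, state both, give the power as about 78%, and change the later 36% to match.
2. In the list of assumptions, say that 140 is the number of respondents per school at follow-up, already net of the 80% response rate, so that the 80% is not read as a further reduction.
3. Keep 6440 as the planned analytic sample in both places where it appears.

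The cost is a wording change. No recruitment target, analysis or outcome definition is affected. Under the 35% option, the only other consequence is a stated power slightly below 80%.
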